### 9.3.1 Side effects of doxycycline:

#### Very frequent (> 10%) side effects:

*Infections and Infestations:* Common cold (22%), influenza symptoms (11%)

*Gastrointestinal:* Nausea (up to 13.4%)

*Nervous system:* Headache (up to 26%)

#### Frequent (1-10%) side effects:

*Metabolic and Nutritional:* Increased blood lactate dehydrogenase (2%), increased blood glucose (1%)

*Respiratory:* Nasopharyngitis (5%), sore throat (5%), sinus congestion (5%), coughing (4%), sinus headache (up to 4%), sinusitis (3%), bronchitis (3%), nasal congestion (2%), pharyngolaryngeal pain (1%)

*Infections and Infestations:* infection (2%), fungal infection (2%), influenza (2%)

*Reproductive Disorders:* Menstrual cramp (4%), bacterial vaginitis (3.3%), vulvovaginal mycotic infection (2%)

*Hepatic and Biliary:* Increased aspartate aminotransferase (2%)

*Body as a whole – general:* Injury (5%), pain (up to 4%), back pain (up to 3%), back ache (2%)

*Dermatologic:* Rash (4%)

*Gastrointestinal:* Vomiting (8.1%), toothache (7%), tooth disorder (6%), dyspepsia (6%), diarrhea (up to 6%), periodontal abscess (4%), acid indigestion (4%), upper abdominal pain (2%), abdominal distention (1%), abdominal pain (1%), stomach discomfort (1%), dry mouth (1%)

*Musculoskeletal:* Joint pain (6%), muscle pain (1%)

*Cardiovascular:* Hypertension (3%), increased blood pressure (2%)

*Psychiatric:* Anxiety (2%)

#### Occasionally (0.1 to < 1%) side effects:

*Gastrointestinal:* Gum pain

#### Rare (< 0.1%) side effects:

*Gastrointestinal:* Adult tooth staining (at least 1 case)

#### Frequency not reported:

*Hematologic:* Hemolytic anemia, thrombocytopenia, neutropenia, eosinophilia

*Metabolic and Nutritional:* Hypoglycemia, anorexia

*Infections and Infestations:* Possible overgrowth of nonsusceptible organisms (superinfection)

*Renal and Urinary:* Dose-related rise in BUN

*Reproductive Disorders:* Vaginal itch, vaginal candidiasis

*Hepatic and Biliary:* Acute hepatocellular injury, cholestatic reactions, hepatotoxicity

*Body as a whole – general:* Microscopic brown-black discoloration of the thyroid gland

*Dermatologic:* Nail discoloration, phototoxicity, photoallergic reaction, photo-onycholysis, photosensitivity, maculopapular and erythematous rashes, erythema multiforme, Stevens-Johnson syndrome, toxic epidermal necrolysis, exfoliative dermatitis, hyperpigmentation

*Gastrointestinal:* Clostridium difficile associated diarrhea, esophageal irritation, ulceration, epigastric burning, black hairy tongue, Esophagitis and esophageal ulcerations (most took medication immediately before going to bed)

*Nervous system:* Sinus headache, dizziness, drowsiness, amnesia, paresthesias of body areas exposed to sunlight, phrenic nerve paralysis after sclerotherapy, benign intracranial hypertension resulting in significant loss of vision

*Ocular:* Diplopia, papilledema, loss of vision (associated with doxycycline-induced benign intracranial hypertension)

*Hypersensitivity:* Hypersensitivity reactions (including urticaria, angioneurotic edema, anaphylaxis, anaphylactoid purpura, serum sickness, pericarditis, exacerbation of systemic lupus erythematosus, drug rash with eosinophilia and systemic symptoms)

*Immunologic:* Autoimmune syndromes

#### Postmarketing reports:

*Nervous system:* Pseudotumor cerebri (benign intracranial hypertension), headache

### 9.3.2 *Precautions to mitigate drug specific risks (Doxycycline)*

#### Photosensitivity

Photosensitivity manifested by an exaggerated sunburn reaction has been observed in some individuals taking tetracyclines. Patients apt to be exposed to direct sunlight or ultraviolet light will be advised that this reaction can occur with tetracycline drugs. Treatment will be immediately stopped at the first evidence of skin erythema.

#### Growth and Development

All tetracyclines form a stable calcium complex in any bone-forming tissue. A decrease in fibula growth rate has been observed in prematures given oral tetracycline in doses of 25 mg/kg every six hours. This reaction was shown to be reversible when the drug was discontinued. Results of animal studies indicate that tetracyclines cross the placenta, are found in fetal tissues, and can have toxic effects on the developing fetus (often related to retardation of skeletal development). Evidence of embryotoxicity also has been noted in animals treated early in pregnancy. If any tetracycline is used during pregnancy or if the patient becomes pregnant while taking these drugs, the patient should be apprised of the potential hazard to the fetus. Therefore women taking part in the clinical trial will be informed in detail about the risk associated with a pregnancy during drug intake. Pregnancy tests will be carried out every week and if a positive pregnancy test occurs against all precautions, treatment will be stopped immediately.

#### *Clostridium difficile* –associated diarrhea

*Clostridium difficile*-associated diarrhea (CDAD) has been reported with the use of nearly all systemic antibacterial agents, including Moxifloxacin, with severity ranging from mild diarrhea to fatal colitis. Therefore participants in this study with diarrhea will be monitored especially for CDAD and in case of suspected or confirmed CDAD treatment will be immediately stopped and the patient will be treated for CDAD as appropriate (fluid and electrolyte management, protein supplementation, antibacterial treatment of *C. difficile*, surgical evaluation if clinically indicated) until recovery. Since CDAD has been reported to occur over two months after the administration of antibacterial agents, patients will be strongly encouraged to report any severe diarrhea to the research team also after completion of the treatment.

#### Superinfection

As with other antibiotic preparations, use of this drug may result in overgrowth of non-susceptible organisms, including fungi. If superinfection occurs, treatment will be immediately stopped and appropriate therapy instituted until recovery.

#### Benign Intracranial Hypertension (pseudotumor cerebri)

Bulging fontanels in infants and benign intracranial hypertension in adults have been reported in individuals receiving tetracyclines. These conditions disappeared when the drug was discontinued. Therefore treatment of

patients with a suspected benign intracranial hypertension (e.g. headache associated with gradual visual field defects, nausea, vomiting, drowsiness) will be stopped immediately and appropriate therapy will be given until full recovery.

#### Pregnancy and breastfeeding:

To avoid any complications, pregnant or breastfeeding women will be excluded from the clinical trial. Pregnancy tests will be carried out during the screening and right before the first treatment. Additionally, pregnancy tests will be repeated at follow-ups. In case of pregnancy in any group, treatment will be stopped immediately. All women will be informed in detail about the risks of getting pregnant during the informed consent procedure and their obligation and responsibility to use effective contraceptive methods excluding daily hormonal contraception as the trial drugs can reduce their efficacy.

Patients with creatinin, AST, ALT, and  $\mu$ -GT levels exceeding two times the upper limit will not be treated with doxycycline. These values will be determined less than one month before doxycycline treatment.

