| Treatment              | 
Doxycycline:
 
 
All individuals of group 1 and 2 as well as double infected individuals (Loa loa in addition to either O. volvulus or M. perstans) will be selected for doxycycline therapy
 
Daily doxycycline therapy for 6 weeks with 200mg
 
Individuals with <math>< 50</math>kg will receive 100mg doxycycline daily for 6 weeks
 
Individuals with <math>< 40</math>kg are excluded
 
                                                                                                                                                                                                                                                                                                                                                                                                                                                                                                                                                                                                                                                                                                                                                                       |

|                    |                                                                                                                                                                                                                                                            |
|--------------------|------------------------------------------------------------------------------------------------------------------------------------------------------------------------------------------------------------------------------------------------------------|
|                    | Albendazole: 
 
• Community based mass drug administration for group 1, 2, 3 and 4
 
• Individuals will receive one dose of 400mg Albendazole every three months with a total of 4 treatments
 
 |
| Time period | 2019-2026                                                                                                                                                                                                                                                  |

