#### **6.5 Analysis whether termination of *Mansonella* and Onchocerciasis infection via 6-week Doxycycline (200mg per day) treatment will change the metabolic and immunological profiles (analysis according to the descriptions above) 12 and 18 months post treatment. Overall timeline of the study**

Patient recruitment & anti-filarial therapy

Follow-up 1 – 12 months after treatment onset

Follow-up 2 – 18 months after treatment onset

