### 9.3 Intervention pilot study

An intervention study analyzing the kinetic of changes in the metabolic and immunological profiles after anti-filarial treatment will be conducted. All patients of the *M. perstans* infected obese and lean subjects will receive anti-filarial therapy (Fig. 1). The known treatment option for *M. perstans* infections with 200mg of doxycycline daily for 6 weeks will be used (28, 29) since ivermectin is known not to deplete the *Mansonella* adult worms and to have only modest effect on microfilariae (30). This doxycycline therapy will permanently sterilize the female adult *Mansonella* worms and lead to the death of the adult worms over time. All onchocerciasis patients will also receive the anti-filarial therapy with 200mg of doxycycline daily for 6 weeks, which was previously shown to sterilize the female adult *Onchocerca* worms and lead to the death of the adult worms over time (31, 32). Patients co-infected with *Onchocerca* and *Mansonella* will also be treated with 200mg of doxycycline daily for 6 weeks. As *L. loa* does not contain *Wolbachia* endosymbionts, doxycycline treatment will not affect *L. loa* co-infection. Onchocerciasis patients, *M. perstans* infected patients, *L. loa* infected individuals and endemic controls will receive single dose of 400 mg albendazole every three months with a total of 4 treatments for the elimination of soil transmitted helminths. Treatment of *L. loa* infected individuals with albendazole does not kill the adult worms, but reduces the microfilariae load in a safe and well tolerated manner. Treatment of onchocerciasis patients with ivermectin as originally intended is not an option, as the study site selected for our study received more than 10 years of ivermectin MDA and suboptimal responses were observed with reoccurring microfilaridermia within less than one month. As a 6-week treatment with doxycycline is not ethically acceptable for endemic controls, those participants will only receive albendazole treatments. Although *Mansonella* infections do not cause pathology and there is no MDA program for mansonellosis we are now treating all *Mansonella* patients with doxycycline. The benefit of the *Mansonella* patients to receive doxycycline may be a lower risk to acquire co-infections such as tuberculosis and HIV. On the other hand we hypothesize that clearance of the *Mansonella* infection by doxycycline therapy may have a negative effect on insulin sensitivity in obese patients, but this needs scientific evidence and was not sufficient to convince the participants of the study not to be treated for the duration of this study. An overview of the groups and subject numbers is provided in Fig.1.

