
Doxycycline (tablets, film-coated) will be administered ad personam by the study clinician directly in the villages under supervision (directly observed treatment, DOT) for 6 weeks. Doxycycline 200mg (2 tablets a 100mg) will be administered orally once daily for 6 weeks. The dosage will be reduced to 1 tablet a 100mg in participants with a body weight  $\geq 40\text{kg}$  and  $< 50\text{kg}$ . Individuals below 40kg will not be treated with doxycycline.

All participants of this study will be also treated by the study clinician directly in the villages under supervision (directly observed treatment, DOT) with 400mg albendazole (one tablet) once every three months for a total of four treatments. This treatment clears intestinal helminths and is used for MDA treatment.

Participants positive for *L. Loa* will receive the above described albendazole treatment and will be followed up on after 12 and 18 months.

All subjects will be followed up at 12 and 18 months after treatment and sample collections as described under 6.2 will be performed. Patients will be screened for helminth infections and the impact of possible re-infections following doxycycline or ivermectin treatment will be taken into account. Compliance to the treatment will be confirmed by collecting empty drug containers during the visit of the study subjects. Subjects will be monitored throughout the study for any adverse effects.

Each treatment will be documented and potential severe adverse events will be documented in the CRF (see Annex CRF).

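### The stop rule for pregnancy reaches albendazole-only women, but no pregnancy test is clearly scheduled before the later albendazole doses

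*Protocol*

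**What the plan says.** Section 9.3.2 of the protocol, under the pregnancy and breastfeeding heading, fixes the tests: "Pregnancy tests will be carried out during the screening and right before the first treatment. Additionally, pregnancy tests will be repeated at follow-ups". The next sentence is the stop rule: "In case of pregnancy in any group, treatment will be stopped immediately".

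Section 8.2 lists the urine dipstick pregnancy test at screening, follow-up 1 and follow-up 2 only. The growth and development paragraph of 9.3.2 adds weekly tests. It names neither the group nor the period, but the paragraph is about tetracyclines and the risk of becoming pregnant while taking the drug.

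Albendazole goes to everyone. The synopsis has "Community based mass drug administration for group 1, 2, 3 and 4", and section 9.3 treats all participants "with 400mg albendazole (one tablet) once every three months for a total of four treatments". Section 9.3 calls doxycycline "not ethically acceptable for endemic controls, those participants will only receive albendazole treatments". Participants with *Loa loa* alone are likewise scheduled for albendazole only.

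Section 6.5 places follow-up 1 at "12 months after treatment onset" and follow-up 2 at 18 months. Section 9.3 words it as "All subjects will be followed up at 12 and 18 months after treatment". No section dates the first albendazole round relative to treatment onset.

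**The concern.** The protocol excludes pregnant women at entry and orders dosing stopped if pregnancy occurs in any group, so it clearly means to prevent dosing in pregnancy. For a woman on albendazole only, albendazole is the only treatment that can be stopped. For a woman on doxycycline, it is the only study drug left after week 6. The rule therefore needs some way of finding a pregnancy before each later albendazole dose.

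The tests listed in 8.2 and in the pregnancy paragraph of 9.3.2 sit at the two ends of the treatment year. A pregnancy that the woman has not recognised or reported could pass through a dosing visit with the plan followed exactly. What is at stake is whether an existing safety rule works in practice, not any estimate, endpoint or error rate.

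**Working it through.** The plan gives no figure to reproduce, so this is a comparison of two timelines.

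**Inputs**
- Albendazole: 4 rounds, 3 months apart, all groups (synopsis; 9.3).
- Doxycycline: 6 weeks, in onchocerciasis, *Mansonella* and co-infected participants (synopsis; 9.3).
- Tests: screening, before first treatment, follow-ups (9.3.2); weekly, read here as the doxycycline course (9.3.2).
- Follow-ups: months 12 and 18 from treatment onset (6.5).
- Offset of round 1 from treatment onset, s: not stated, so it is varied.

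**Formula.** Round k falls at month s + 3(k − 1). One month is 52/12 weeks.

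**Base case, s = 0.** Rounds fall at months 0, 3, 6 and 9 (weeks 0, 13, 26, 39).
- Rounds with no preceding test since the first dose or the doxycycline course: 3/4 = 75%.
- First follow-up test minus last dose: 12 − 9 = 3 months. Second: 18 − 9 = 9 months.

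| Time since last listed test | Round 2 | Round 3 | Round 4 |
|---|---|---|---|
| Albendazole only (last test week 0) | 13 weeks | 26 weeks | 39 weeks |
| Doxycycline-treated (last test week 6) | 13 − 6 = 7 weeks | 26 − 6 = 20 weeks | 39 − 6 = 33 weeks |

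**Other readings**
- Round 1 at week 6, after doxycycline: rounds at weeks 6, 19, 32 and 45. Round 1 has a weekly test; rounds 2 to 4 do not. The last dose still precedes follow-up 1 at week 52.
- Round 1 at month 3 in doxycycline-treated women: rounds at months 3, 6, 9 and 12. Rounds 1 to 3 are untested, and round 4 could coincide with follow-up 1. The count is still 3 of 4, but the rounds differ. In albendazole-only women the first albendazole dose is the first treatment, so it is tested and the next three are not.
- A tested visit at month 6, with s = 0, if the 6-month interval in section 6.4 were taken to include pregnancy tests: rounds 2 and 4 are untested, 2/4.
- Follow-up counted from the end of treatment, as section 9.3 could be read: both follow-up tests move later, so they come no closer to the doses.
- Weekly tests taken literally, for all women throughout: every round is preceded by a test and there is no gap. The lists in 8.2 and in the pregnancy paragraph of 9.3.2 would then both leave out most of the testing.

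**Tests per woman now.** Albendazole only: 1 + 1 + 2 = 4. Doxycycline-treated: 1 + 1 + 6 + 2 = 10.

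**The case against.** The strongest objection is the weekly-testing sentence. It carries no end date and no group limit, and the sentence before it speaks of women in the trial generally. Read literally, it closes the gap. This stands as a reason not to say flatly that no test precedes rounds 2 to 4. The tetracycline context makes the 6-week reading the natural one, but the protocol does not say so.

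The date of round 1 is also missing, and follow-up timing varies between sections (12-month intervals in 6.2, 6-month in 6.4, months 12 and 18 in 6.5). This stands too: which rounds are untested, and whether the follow-up tests all come after the last dose, depends on it. Of the dated readings above, none leaves fewer than two rounds untested.

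The case report form annex is not shown and might include a check at each dosing visit. That cannot be settled here; the schedules in the protocol body do not mention one.

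Other safeguards exist. Section 7.2 makes contraception for the whole treatment period an entry condition. Section 9.3.2 asks for effective methods "excluding daily hormonal contraception as the trial drugs can reduce their efficacy". Albendazole is given under direct observation by the study clinician, and section 9.3.5 requires questioning and examination at each contact. So the stop rule can still be triggered by a known or reported pregnancy. These measures lower the risk but do not detect an unrecognised pregnancy.

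A reader might also infer a known fetal hazard from albendazole. The documents do not support that: 9.3.2 describes one for tetracyclines, and the albendazole side-effect list in 9.3.3 contains none.

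**Conclusion.** The point holds in a conditional form. The stop rule covers albendazole-only women. If the weekly tests belong to the 6-week doxycycline course and albendazole starts at or near treatment onset, no listed test precedes rounds 2 to 4 (3 of 4 rounds), and the follow-up tests arrive when no dose is left to withhold. With a month-3 start in doxycycline-treated women the untested rounds are 1 to 3; with a tested month-6 visit they number two.

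By the synopsis, the endemic control and loiasis groups are planned at 2 × 400 = 800. Those co-infected with *O. volvulus* or *M. perstans* would also get doxycycline, and the share of women is not stated. The documents give no basis for estimating how many pregnancies would be missed.

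It would go too far to conclude that the stop rule cannot work at all, that fetal harm is shown, or that the trial's results are affected. Known pregnancies still trigger the rule, and neither the HOMA-IR comparison nor its power depends on this. The importance is low to moderate, and the case for change rests on the protocol's own safety intention and the small cost.

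**What to change.** Put one combined schedule for women of childbearing potential, in all groups, into 8.2 and 9.3.2:
- urine dipstick at screening and before the first dose of any study drug;
- weekly during the 6-week doxycycline course, in doxycycline-treated women;
- before each albendazole dose, in every group;
- at follow-ups 1 and 2.

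State that the stop rule includes albendazole-only participants. State also that a positive test withholds that dose and all later study doses while the woman stays in follow-up, as section 9.11.2 already encourages after withdrawal from treatment. Give the date of the first albendazole round relative to treatment onset.

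Cost: up to three extra dipsticks per woman, from 4 to 7 on albendazole only and from about 10 to 13 with doxycycline. Even if every participant were such a woman, the ceiling is 3 × 1600 = 4800 using the four groups of 400 in the synopsis, or 3 × 1200 = 3600 using the total of 1200 that the synopsis also gives. The trial already uses this test, and it would be done at supervised dosing visits, so no new visit or invasive procedure is needed. The real burdens are privacy and counselling in the village at each round, and the albendazole doses missed after a positive test.

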#### *9.3.3 Side effects of Albendazole*

Very frequent (> 10%) side effects:

Hepatic: Elevated liver enzymes (up to 16%, mostly mild to moderate)

Nervous system: Headache (up to 11%)

#### Frequent (1-10%) side effects:

Dermatologic: Reversible alopecia (thinning of hair, moderate hair loss)

Gastrointestinal: Epigastric / abdominal pain, nausea, vomiting, upper gastrointestinal (GI) symptoms, GI disturbances

Hematologic: Leukopenia

Nervous system: Raised intracranial pressure, dizziness, neurological events

Other: fever, hyperpyrexia

#### Occasionally (0.1 to < 1%) side effects:

Dermatologic: itchiness, skin rashes

Gastrointestinal: diarrhea

Hepatic: hepatitis

Hypersensitivity: hypersensitivity reactions (including rash, pruritus, urticaria)

Nervous system: vertigo, meningeal signs

